## Abstract

**Background:**

Diabetic kidney disease (DKD) is a significant complication of diabetes and has garnered considerable attention. Our previous retrospective study indicated that Shenzhuo formula (SZF) potentially reduces macroalbuminuria secondary to DKD.

**Methods:**

This trial is a 24-week, randomized, multicentric, double-blinded, double-dummy clinical trial. A total of 120 patients with DKD will be equally and randomly divided into two groups: SZF+ irbesartan simulator or irbesartan + SZF simulator. The 24-h urinary protein change from baseline to week 24 is the primary outcome measure. The secondary outcome measures include serum creatinine, estimated glomerular filtration rate, urinary albumin excretion rate, improvement in traditional Chinese medicine symptoms, fasting blood glucose, 2-h postprandial plasma glucose, hemoglobin A1c, cholesterol, triglycerides, high density lipoprotein, low density lipoprotein, blood pressure, albumin to creatinine ratio, and the Audit of Diabetes-Dependent Quality of Life 19. Our recruitment began in May 2015; currently, we have recruited 100 participants, with a designed maximum sample size of 120. The interim results were reviewed at *N* = 60, and continuing recruitment was recommended. This statistical analysis plan includes our approach to missing data imputation, primary and secondary outcomes analyses, and safety endpoints.

**Discussion:**

This statistical analysis plan will standardize the clinical trial’s statistical analysis and avoid outcome selective reporting bias and data-driven analysis. This trial will provide further clinical evidence regarding the effectiveness of SZF in managing macroalbuminuria secondary to DKD.

**Trial registration:**

Chinese Clinical Trial Registry ChiCTR-ICR-15006311. Registered on 26 May 2013. http://www.chictr.org.cn/showproj.aspx?proj=10862

**Supplementary Information:**

The online version contains supplementary material available at 10.1186/s13063-021-05961-8.

## Background

Diabetic kidney disease (DKD) is a leading cause of chronic kidney disease (CKD) in developed countries and is rapidly becoming the leading cause in developing countries as well [1]. It is one of the most common complications of diabetes mellitus affecting approximately 20–40% of diabetic patients in China; furthermore, it has replaced chronic glomerulonephritis as the leading cause of end-stage renal disease in middle-aged and elderly patients [2–4]. To address this, renin-angiotensin-aldosterone system (RAAS) inhibitors have recently been used; however, the prevalence of DKD remains unchanged [5, 6]. Therefore, exploring effective drugs for preventing DKD occurrence and development is critical.

Recently, increasing extensive clinical experience has supported the use of traditional Chinese medicine (TCM) for DKD. TCM with angiotensin receptor inhibitor treatment can reduce proteinuria in patients with type 2 diabetes [7]. Our previous retrospective study found that the Shenzhuo formula (SZF) improves glomerular filtration rate (GFR) and reduces 24-h urinary protein (24 h-UP) [8]. Another study of 88 patients with DKD found that the SZF improved estimated glomerular filtration rate (eGFR) and slowed DKD progression [8].

A previous study evaluated the 2-year effectiveness of SZF in the treatment of DKD and showed similar results with no significant changes in liver function and routine blood test results compared with the baseline; additionally, no patient experienced discomfort or severe adverse events [9].

However, comparisons between the effectiveness of SZF and RAAS inhibitors in patients with DKD remain lacking. Therefore, we designed and implemented a trial to investigate the effectiveness and safety of SZF and irbesartan in treating patients with DKD and macroalbuminuria. We hypothesized that SZF alone can improve macroalbuminuria secondary to DKD. Using SZF, we conducted a 24-week, randomized, multicentric, double-blinded, double-dummy, controlled clinical trial. The research protocol was previously reported [10]. The original protocol provides more details regarding the trial rationale, eligibility criteria, interventions, concomitant treatments, study visits, and data management.

Here, we describe the study’s pre-determined statistical analysis plan (SAP). To prevent reporting bias and data-driven interpretation, the SAP will be applied at the termination of the trial. The SAP (version 2.0 20180626) was completed before the data analysis, and the investigators adhered to the requirements in data analysis, according to “Guidelines for the Content of Statistical Analysis Plans in Clinical Trials” published in JAMA [11] (see Additional file 1 populated checklist). It includes our approach to imputing missing data and analyzing primary and secondary outcomes; additionally, safety and baseline analysis was conducted, and total adverse effects were analyzed.

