## Statistical principles

### Overall principles

After completion of the trial, all the statistical analysis tests will use two-sided tests with a nominal alpha level of 0.05, using the SAS [10, 12]. All confidence interval (CI) reports will be 95% CIs. For each outcome, the null hypothesis is the absence of difference between the intervention groups.

The description of measurement indicators will calculate the mean, standard deviation, median, minimum, maximum, and interquartile range (Q3–Q1). Normal continuous variables will be presented as the mean and standard deviation; non-normally distributed continuous variables will be presented as median with interquartile range. Counting indicators will be presented as the frequency and percentage of each category.

Inter-group comparisons will be performed with independent two-sample *t*-tests (normality, homogeneity of variance) or Wilcoxon rank-sum test (non-normality, heterogeneity of variance). Comparisons within normal and nonnormally distributed groups will be performed using paired *t*-test and paired rank-sum test, respectively. *χ*^2^ test or Fisher’s exact probability will be needed for count metrics, and the Wilcoxon rank-sum test will be used for categorical variables. A generalized linear mixed model analysis will be performed on the repeated measured outcome.

In situations where an imbalance in the baseline indicators exists, an adjustment will be required for the efficacy comparison of variables, such as age, sex, and concomitant treatment. The covariance method will be used for continuous variables, and logistic regression analysis was used for count metrics and hierarchical metrics.

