## Analysis methods

### Outcome measure analyses

#### Primary outcome analyses

The primary analysis will be conducted in the FAS and PPS. The change in 24-h UP (mg/24 h) is the primary outcome. The distribution and changes of 24-h UP at weeks 0, 4, 8, 12, 16, 20, and 24 of medication will be described. Intra- and inter-group comparisons will be made. The distributions of qualitative judgments of 24-h UP at weeks 4, 8, 12, 16, 20, and 24 will be described and compared between groups. The baseline 24-h UP is essential to assess the progression of UP; therefore, analysis of covariance (ANCOVA) will be performed to analyze the 24-h UP change from baseline to week 24, using baseline 24-h UP as a covariate. Interactions between site and group will also be tested.

Table 3 provides a reference for the qualitative determination of the variation. The efficiency rate will be calculated by summing the rate of clinical control, obvious therapeutic effect, and therapeutic effect (Table 4).

**Table 3 Tab3:** 24-h UP qualitative judgments classification standard

Qualitative judgment	Standard
Clinical control	24-h UP< 0.5 g
Obvious therapeutic effect	24-h UP reduction ≥ 50%
With therapeutic effect	24-h UP reduction ≥ 20%
Invalid	Fail to reach the standards above

**Table 4 Tab4:** Analysis of primary outcome

Time point	SZF, number, mean (SD)	Irbesartan, number, mean (SD)	Mean difference (95% CI)	***p*** value
Visit at	*n* = xx	*n* = xx		
Week 0	xx (xx)	xx (xx)	xx (xx to xx)	.xx
Week 4 ^a^	xx (xx)	xx (xx)	xx (xx to xx)	.xx
Week 8	xx (xx)	xx (xx)	xx (xx to xx)	.xx
Week 12	xx (xx)	xx (xx)	xx (xx to xx)	.xx
Week 16	xx (xx)	xx (xx)	xx (xx to xx)	.xx
Week 20	xx (xx)	xx (xx)	xx (xx to xx)	.xx
Week 24	xx (xx)	xx (xx)	xx (xx to xx)	.xx
Overall SZF effect^b^				.xx

^a,b^*p* values comparing between group differences at visit points post-randomization (a) and over the entire24-week trial (b: primary outcome)

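### The stated hypothesis is that SZF alone improves macroalbuminuria, but the plan tests only whether SZF differs from irbesartan; neither a non-significant difference nor a within-arm fall can support it

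*Protocol article*

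**What the plan says.** The Background gives the motive as comparative: "comparisons between the effectiveness of SZF and RAAS inhibitors in patients with DKD remain lacking". The hypothesis that follows is absolute: "We hypothesized that SZF alone can improve macroalbuminuria secondary to DKD". It names no comparator and no margin.

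The abstract gives the arms as "SZF+ irbesartan simulator or irbesartan + SZF simulator". There is no placebo-only or untreated arm.

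Overall principles specifies "two-sided tests with a nominal alpha level of 0.05" and then: "For each outcome, the null hypothesis is the absence of difference between the intervention groups". The primary test follows that rule: "analysis of covariance (ANCOVA) will be performed to analyze the 24-h UP change from baseline to week 24", with baseline 24-h UP as covariate.

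Within-arm tests are planned as well. Overall principles: "Comparisons within normal and nonnormally distributed groups will be performed using paired" t-tests or paired rank-sum tests. Primary outcome analyses: "Intra- and inter-group comparisons will be made". Secondary outcome analyses likewise plans comparisons both between and within groups. In Table 6 (TCM syndrome scores) every p-value compares week 0 with week 24 inside one arm.

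**The concern.** The hypothesis needs a contrast between SZF and no active treatment, and no arm supplies one. The controlled contrast is with an active drug, tested against a null of no difference. Rejecting that null says the drugs differ. Failing to reject it says neither that SZF is effective nor that it is similar to irbesartan.

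The only planned tests that do not set SZF against irbesartan are the within-arm paired tests. They look as if they answer the hypothesis, but they attribute to SZF every change since baseline, whatever its cause. At stake is what the trial may conclude if the arms do not differ significantly and 24-h UP falls in both.

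**Working it through.** No figure in the plan is in dispute. The total of 120 cannot be reproduced, because the sample size calculation is deferred to an earlier protocol article that is not shown. The check is one of logic, with illustrative sizes.

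**1. Questions against planned tests**

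| Question | What it needs | Planned here? |
|---|---|---|
| Does SZF work? | SZF against no active treatment | No such arm |
| Does SZF differ from irbesartan? | Between-arm test | Yes: ANCOVA, mixed model, response classes compared between arms |
| Is SZF as good as irbesartan? | A margin and a matching test | No; the null is no difference for each outcome |
| Did 24-h UP change on SZF? | Paired test | Yes, but uncontrolled |

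**2. What a non-significant difference leaves open.** 120 patients at 1:1 give 60 per arm. In units of the SD of change, unadjusted for baseline:

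- 95% CI half-width = 1.96 × √(2/60) = 0.36 SD.
- Detectable difference at 80% power = (1.96 + 0.84) × √(2/60) = 0.51 SD.

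An observed difference of zero is still compatible with either drug being better by up to 0.36 SD. ANCOVA would narrow this by an amount that the document does not allow one to compute.

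**3. Within-arm test of an inert drug under a shared drift.** Assume that both arms fall by x SD from causes other than the drug. Then P(significant) = Φ(x√60 − 1.96) + Φ(−x√60 − 1.96).

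- x = 0.1: 0.12
- x = 0.2: 0.34
- x = 0.3: 0.64

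The two-sided nominal rate is 0.05. The between-arm test stays at 0.05, because the drift cancels.

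**4. Regression to the mean alone.** All inputs are assumed: entry at 24-h UP of at least 0.5 g (borrowed from the clinical control class in Table 3; the eligibility section says only macroalbuminuria), median 0.8–1.2 g, between-person log-SD 0.7, within-person log-SD 0.2–0.5, 60 patients, no drug effect, and the qualifying value used as baseline. The probability of a significant fall, against 2.5% nominal in that direction, is:

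- paired t on mg/24 h: about 3–8%;
- signed-rank on mg/24 h: about 4–16%.

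Repeat simulation moves the upper ends by a point or two. If baseline is a collection separate from the qualifying one, the rate returns to about 2.5%. The document does not say which applies.

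**5. The pattern that would mislead.** Assume SZF is inert, both arms drift by 0.3 SD, and irbesartan is better by a further 0.2, 0.3 or 0.4 SD. In simulation, a non-significant between-arm test together with a significant fall on SZF occurs in about 58%, 50% or 37% of trials.

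**The case against.** The strongest defence is that the comparative aim is already clear. It stands just before the hypothesis, every null is between groups, and the primary test is a between-arm ANCOVA. The word alone may simply mean monotherapy, as opposed to the combination with an angiotensin receptor inhibitor cited earlier in the Background. Tables 4 and 5 already show the mean difference, its 95% CI and between-arm p-values. The earlier protocol article may set out the objective in full, and a condensed article often leaves out how a null result will be worded.

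Much of this stands. For 24-h UP the planned display is already the right one, and within-arm testing enters only through the text of the methods sections. The defence does not remove the mismatch. Even read as monotherapy, the hypothesis asserts an improvement that no planned contrast can show if the arms do not differ. If the earlier article held a margin, the null stated here for each outcome would contradict it.

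Two stronger readings are tempting. A reader might infer that a null result will be turned into an efficacy claim through the paired tests; the document nowhere says so. A reader might also quote false-positive rates of 5–35% from regression to the mean. Those arise on a log scale, whereas the plan analyses mg/24 h and states no transformation.

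**Conclusion.** The point holds as a mismatch between the hypothesis and the tests. As written, neither a non-significant between-arm result nor a significant within-arm fall can support the stated hypothesis. A significant result in favour of SZF would support it indirectly, on the premise that irbesartan is no worse than placebo, so the defect matters chiefly if the arms do not differ significantly.

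The direction of the within-arm bias is clear wherever there is a downward drift or selection on baseline. Its size is not: regression to the mean may add nothing or take the rate to the upper ends in step 4, and the larger figures in steps 3 and 5 rest entirely on assumed drifts. The correction is worth making because it is cheap and settles in advance what may be concluded.

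**What to change.** - **Background:** restate the hypothesis as the one tested, that SZF and irbesartan differ in the change in 24-h UP from baseline to week 24.
- **Overall principles:** add that efficacy conclusions rest on the between-arm estimate and its 95% CI, and that a non-significant difference will be reported as inconclusive, not as equivalence or non-inferiority.
- **Overall principles, primary and secondary outcome analyses:** make the within-arm comparisons descriptive, giving change with a 95% CI and no test.
- **Table 6:** replace the within-arm p-values with between-arm comparisons. Tables 4 and 5 need no change on this point, as their p-values are already between arms.

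The cost is wording and one table shell; design, data collection and the primary ANCOVA are untouched. The sponsor gives up within-arm efficacy claims, which the design could not support.

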## Study methods

### Trial design

The SZF clinical trial will be conducted in 11 centers and will recruit 120 patients with macroalbuminuria secondary to DKD. In the protocol, we specified 120 subjects from nine hospitals will be included. However, three centers have been deleted because they have not carried out patient recruitment; in addition, we added five centers to hasten the trial. These hospitals include The Second Affiliated Hospital of Shaanxi University of TCM, Xianyang; Zhengzhou Hospital of TCM, Zhengzhou; Hangzhou Hospital of TCM, Hangzhou; The Affiliated Hospital to Changchun University of Chinese Medicine, Changchun; and Zhejiang Hospital of TCM, Hangzhou. The newly added centers have passed the ethical review by the Ethics Committee of Guang’anmen Hospital. To ensure quality, all investigators will receive intensive training regarding the conduct of the research and intervention before recruitment. The flow diagram shown in Fig. 1 provides a brief description of the research process. Our previous protocol defines the sample size calculation [10].

**Fig. 1 Fig1:**
[figure not shown]
Flow diagram of the study

### Randomization and blinding

Eligible patients will be randomized in a 1:1 allocation ratio using a central permuted block randomization procedure (block size 4) with block sizes. The groups will include the TCM group, which will receive SZF and stimulated irbesartan, and the Western medicine group, which will receive SZF simulation agents and irbesartan capsules. Using the PROC PLAN process statement of SAS 9.4 (SAS/STAT Software 9.4, SAS Institute, Inc., Cary, NC, USA), a random arrangement (random coding table) of 120 subjects will be generated according to the number of seeds. The Institute of Basic Research in Clinical Medicine of the China Academy of Chinese Medical Sciences provides the random arrangement, 24-h emergency code break, and medical information. Participants, investigators, and statisticians will be blinded to treatment assignments.

SZF drugs and SZF simulators have identical shape, smell, and color, which were consistent when dissolved in water. Irbesartan capsules and simulators had consistent scent and appearance when the capsule was opened.

### Interim analysis

Independent biostatisticians will perform interim analysis once 60 patients complete the 24-week treatment, which is 50% of the planned number of patients. The primary and secondary outcomes and safety assessments will be evaluated to compare the effects and safety of SZF and irbesartan. The Data Monitoring Committee would recommend continuing, discontinuing, or modifying the trial, if concerns regarding the effect and safety of the participants will arise.

A recommendation of trial termination would be considered by the data management, clinical trial institutions, ethics committees, and sponsors if achieving the difference in treatment effects is unlikely or if intolerable adverse effects occurred. The detailed results remain confidential to the investigators. The interim analysis was conducted in September 2018, and continued recruitment was recommended.

### Criteria for trial discontinuation

Trial abortion refers to premature discontinuation of the clinical trial. The purpose of trial abortion is to protect subject equity, guarantee trial quality, and avoid unnecessary economic losses. The trial will be terminated if any of the following situations occur:

(1) Serious safety issues occurring during the trial warrant prompt discontinuation.

(2) Drug treatments found to be significantly inadequate or even ineffective in the trial to be of clinical value should be suspended, to avoid patient treatment delays and economic losses.

(3) The clinical trial protocol is found to have a significant lapse or a well-designed protocol that has undergone substantial deviations in implementation, increasing the difficulty in evaluating the drug effect.

(4) The sponsor requests discontinuation (e.g., reasons for funding, administration, etc.).

(5) Withdrawal of the trial by the administration.

## Statistical principles

### Overall principles

After completion of the trial, all the statistical analysis tests will use two-sided tests with a nominal alpha level of 0.05, using the SAS [10, 12]. All confidence interval (CI) reports will be 95% CIs. For each outcome, the null hypothesis is the absence of difference between the intervention groups.

The description of measurement indicators will calculate the mean, standard deviation, median, minimum, maximum, and interquartile range (Q3–Q1). Normal continuous variables will be presented as the mean and standard deviation; non-normally distributed continuous variables will be presented as median with interquartile range. Counting indicators will be presented as the frequency and percentage of each category.

Inter-group comparisons will be performed with independent two-sample *t*-tests (normality, homogeneity of variance) or Wilcoxon rank-sum test (non-normality, heterogeneity of variance). Comparisons within normal and nonnormally distributed groups will be performed using paired *t*-test and paired rank-sum test, respectively. *χ*^2^ test or Fisher’s exact probability will be needed for count metrics, and the Wilcoxon rank-sum test will be used for categorical variables. A generalized linear mixed model analysis will be performed on the repeated measured outcome.

In situations where an imbalance in the baseline indicators exists, an adjustment will be required for the efficacy comparison of variables, such as age, sex, and concomitant treatment. The covariance method will be used for continuous variables, and logistic regression analysis was used for count metrics and hierarchical metrics.

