#### Secondary outcome analyses

The secondary outcome of the FAS and PPS will be analyzed, including serum creatinine (SCr, umol/L), eGFR (mL/(min×1.73 m^2^) using CKD-EPI creatinine equation [13]), urinary albumin excretion rate (μg/min), improvement in TCM symptoms, fasting blood glucose (mmol/L), 2-h postprandial plasma glucose (mmol/L), HbA1C (%), cholesterol (mmol/L), triglycerides (mmol/L), high density lipoproteins (mmol/L), low density lipoproteins (mmol/L), blood pressure (mmHg), albumin to creatinine ratio (ACR, mg/g), and the audit of diabetes-dependent quality of life 19 (ADDQoL) [14] The distribution and changes of all the secondary outcomes at the baseline and at each visit point will be compared between and within groups (Table 5).

**Table 5 Tab5:** Secondary outcome analysis

Time point	SZF, number, mean (SD)	Irbesartan, number, mean (SD)	Mean difference (95% CI)	***p*** Value
Scr at	*n* = xx	*n* = xx		
Week 0	xx (xx)	xx (xx)	xx (xx to xx)	.xx
Week 4	xx (xx)	xx (xx)	xx (xx to xx)	.xx
Week 8	xx (xx)	xx (xx)	xx (xx to xx)	.xx
Week 12	xx (xx)	xx (xx)	xx (xx to xx)	.xx
Week 16	xx (xx)	xx (xx)	xx (xx to xx)	.xx
Week 20	xx (xx)	xx (xx)	xx (xx to xx)	.xx
Week 24	xx (xx)	xx (xx)	xx (xx to xx)	.xx
Overall SZF effect ^a^				.xx
eGFR at	*n* = xx	*n* = xx		
Week 0	xx (xx)	xx (xx)	xx (xx to xx)	.xx
Week 4	xx (xx)	xx (xx)	xx (xx to xx)	.xx
Week 8	xx (xx)	xx (xx)	xx (xx to xx)	.xx
Week 12	xx (xx)	xx (xx)	xx (xx to xx)	.xx
Week 16	xx (xx)	xx (xx)	xx (xx to xx)	.xx
Week 20	xx (xx)	xx (xx)	xx (xx to xx)	.xx
Week 24	xx (xx)	xx (xx)	xx (xx to xx)	.xx
Overall SZF effect				.xx
UAER at	*n* = xx	*n* = xx		
Week 0	xx (xx)	xx (xx)	xx (xx to xx)	.xx
Week 4	xx (xx)	xx (xx)	xx (xx to xx)	.xx
Week 8	xx (xx)	xx (xx)	xx (xx to xx)	.xx
Week 12	xx (xx)	xx (xx)	xx (xx to xx)	.xx
Week 16	xx (xx)	xx (xx)	xx (xx to xx)	.xx
Week 20	xx (xx)	xx (xx)	xx (xx to xx)	.xx
Week 24	xx (xx)	xx (xx)	xx (xx to xx)	.xx
Overall SZF effect				.xx
FBG	*n* = xx	*n* = xx		
Week 0	xx (xx)	xx (xx)	xx (xx to xx)	.xx
Week 4	xx (xx)	xx (xx)	xx (xx to xx)	.xx
Week 8	xx (xx)	xx (xx)	xx (xx to xx)	.xx
Week 12	xx (xx)	xx (xx)	xx (xx to xx)	.xx
Week 16	xx (xx)	xx (xx)	xx (xx to xx)	.xx
Week 20	xx (xx)	xx (xx)	xx (xx to xx)	.xx
Week 24	xx (xx)	xx (xx)	xx (xx to xx)	.xx
Overall SZF effect				.xx
2hPG at	*n* = xx	*n* = xx		
Week 0	xx (xx)	xx (xx)	xx (xx to xx)	.xx
Week 4	xx (xx)	xx (xx)	xx (xx to xx)	.xx
Week 8	xx (xx)	xx (xx)	xx (xx to xx)	.xx
Week 12	xx (xx)	xx (xx)	xx (xx to xx)	.xx

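### Unequal variance alone switches visit-level comparisons to the Wilcoxon rank-sum test, which assumes equal spread under its null and does not test the mean difference printed beside it

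*Protocol article*

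**What the plan says.** Overall principles (protocol article, Statistical principles) ties the independent two-sample t-test to "normality, homogeneity of variance" and gives the alternative as the "Wilcoxon rank-sum test (non-normality, heterogeneity of variance"). No unequal-variance t-test is named. All tests are "two-sided tests with a nominal alpha level of 0.05", and for each outcome "the null hypothesis is the absence of difference between the intervention groups"; no parameter is specified.

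The result tables are fixed in advance. Table 4 (24-h UP) and Table 5 (secondary outcomes) show mean (SD) per arm, a "Mean difference (95% CI") column and a p-value at each visit. Table 4's footnote describes its visit-level p-values as "values comparing between group differences at visit points post-randomization (a"). For the secondary outcomes, "The distribution and changes of all the secondary outcomes at the baseline and at each visit point will be compared between and within groups".

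Two analyses have their own method. For the primary outcome, "analysis of covariance (ANCOVA) will be performed to analyze the 24-h UP change from baseline to week 24", with baseline 24-h UP as covariate. Repeated outcomes also receive a generalized linear mixed model.

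**The concern.** The null distribution of the rank-sum test assumes that the two arms are exchangeable, so they share spread as well as location. Unequal variance is evidence against that assumption. It is therefore a reason to avoid reading the rank-sum p-value as a statement about location, not a reason to adopt the test.

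The table layout makes this visible. The estimate and CI concern means, while the p-value concerns whether one arm tends to give larger values than the other. With equal spread and similar shape these usually agree. With unequal spread they need not, and a reader could see a CI excluding zero beside a non-significant p-value, or the reverse. Unequal spread is plausible here: the arms receive different kinds of drug, and a subgroup may respond strongly to one of them.

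**Working it through.** The article gives no SD, effect size or power, so there is no planned figure to reproduce. The check compares the rank-sum test with Welch's t-test by simulation.

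**Inputs from the article.** 120 patients allocated 1:1, so 120 / 2 = 60 per arm; two-sided 0.05.

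**Assumptions.** Distributions, SD ratios and the 60/45 split. The table CI is taken to be Welch's, so a conflict between p-value and CI means that the two tests disagree on significance.

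**Formula.** Welch: t = (m1 − m2) / √(s1²/n1 + s2²/n2), with Satterthwaite degrees of freedom. The rank-sum test uses the normal approximation.

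**Step 1: reach.** Table 5 has seven outcomes at seven visits (SCr, eGFR, UAER, FBG, 2hPG, BP, ACR) and six at three visits (TC, TG, LDL, HDL, HbA1c, ADDQoL). Post-baseline rows: 7 × 6 + 6 × 2 = 54. Table 4 adds 6, making 60 comparisons in each of FAS and PPS.

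**Step 2: type I error, normal data, equal means (20,000 runs).**

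| SD ratio | Rank-sum 60/60 | Rank-sum 60/45, larger SD in smaller arm | Welch, both layouts |
|---|---|---|---|
| 1.5 | 5.3% | 6.1% | 5.0-5.1% |
| 2 | 6.0% | 6.8% | 5.0% |
| 3 | 7.2% | 8.4% | 5.0-5.3% |
| 4 | 7.4% | 9.1% | 4.8% |

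With the larger SD in the larger arm (45/60), the rank-sum rate is 4.3-5.4%.

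**Step 3: runs where unequal variance alone triggers the switch** (60/60; Shapiro-Wilk passed in both arms, variance test failed; 4,000 runs). The rank-sum test rejects 4.5%, 6.5% and 6.8% at SD ratios 1.5, 2 and 3. Welch rejects 4.2%, 5.3% and 5.5%.

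**Step 4: true mean difference, normal data, 60/60.** The assumed difference is half the root-mean-square SD (6,000 runs). At SD ratio 3, power is 73.5% for rank-sum and 76.5% for Welch: 76.5 − 73.5 = 3.0 points. The tests disagree in roughly 7-11% of runs across SD ratios 1.5 to 3. For scale, with equal SDs they disagree in about 6% of runs, and rank-sum is about 2.5 points less powerful. Part of the gap is therefore the ordinary cost of ranking normal data; under equal variances the plan would use the t-test and avoid it.

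**Step 5: mild responder mixture, 60/60.** In one arm 40% improve by 1.2 and the rest by 0; the other arm improves by 0.24 throughout; residual SD is 0.6. The true difference is 0.40 × 1.2 − 0.24 = 0.24. In 64% of runs both arms pass Shapiro-Wilk and the variance test fails, so unequal variance alone causes the switch. Power over all runs is 33% for rank-sum and 43% for Welch: 43 − 33 = 10 points. The tests disagree in about 10% of the switched runs.

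**The case against.** **The trial's main inferences lie elsewhere.** The week-24 primary change goes to ANCOVA and repeated outcomes to a mixed model. This stands: a reader might infer that the primary result is exposed, and the article does not support that. If the visit-level p-values were meant to be mixed-model contrasts, the rule would matter less still. But the article does not say so, and the outcome sections name no other test for the visit-level comparisons of the secondary outcomes.

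**Skewed urinary protein could produce far larger errors.** A reader might infer severe inflation or loss of power from log-normal data or a strong 35% responder mixture. Those results cannot be charged to this trigger. With Shapiro-Wilk at 0.05 as an assumed normality check, 100% of the log-normal runs and 97% of the mixture runs are flagged as non-normal, so the plan sends them to the rank-sum test anyway. Deleting the variance criterion would leave them essentially unchanged.

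**The stated null names no mean, and non-normal variables are to be shown as median with interquartile range.** Both are true. The rank-sum test is valid for identical distributions, so part of the problem is a mismatch between p-value and estimate. But approximately normal data with unequal variance keep the mean (SD) display and still receive a rank-sum p-value.

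**The two triggers might be meant jointly.** Then normal data with unequal variance would have no assigned test, because the t-test requires equal variance. The same amendment closes that gap.

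**Arms as unequal as 60/45 are unlikely under 1:1 allocation in blocks of four.** Fair for randomization; that split is a sensitivity case for uneven dropout.

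**Conclusion.** The point holds at modest size. The stated rule chooses a poor remedy for unequal variance and separates the p-value from the estimate shown with it. It is confined to unadjusted visit-level comparisons of 24-h UP and the secondary outcomes, in both analysis sets. At 60 per arm with near-normal data, the excess type I error is at most about 2 percentage points up to a threefold SD ratio, and about 3 points at 60/45 when the smaller arm has the larger spread. The more practical costs are some lost power and occasional contradiction between p-value and CI. All of these sizes rest on assumed distributions and SD ratios, because the article supplies no variance information. The amendment is worth making because it is simple and nearly free, not because the trial's conclusion is at risk.

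**What to change.** Amend the sentence on inter-group comparisons in Overall principles:

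- Delete unequal variance from the rank-sum criteria. For approximately normal continuous outcomes, use the Welch unequal-variance t-test with its 95% CI for the mean difference, and carry out no preliminary variance test.
- Where the rank-sum test is kept for non-normal outcomes, report median (IQR) per arm and the Hodges-Lehmann shift with its 95% CI in place of the mean difference. Add a matching alternative layout to Tables 4 and 5.

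The ANCOVA and mixed-model text need not change for this point. The cost is a wording change, an alternative table column and a different line of SAS output. The loss of power when variances are in fact equal is negligible: at 60 per arm with equal-variance normal data, Welch and the pooled t-test both had 77% power in the simulated case.
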